## **OUTCOMES**

### Primary outcome:

The primary outcome is self- and observer-rated assessment of depressed mood (primary outcome) as measured by the POMS and observer-rated depressed mood and depressive symptom severity as measured by the MADRS in response to endotoxin (0.8 ng/kg body weight) vs. placebo with repeated assessment over up to 12 hours. Both the POMS and MADRS have been found to be sensitive to acute changes in depressed mood following endotoxin.

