Endotoxin is a model of systemic inflammation that can be used to experimentally interrogate the role of inflammation to induce depressive symptoms. Endotoxin resembles a pathogen-induced, naturally occurring inflammatory immune response, which is driven by a complex interplay of various cytokines, all with distinct kinetics and locally differing concentrations. Injection of a single cytokine does not model this response as it does not target the inflammatory cascade. Likewise, acute laboratory-based stress can activate inflammation, but only induces modest inflammatory and depression responses, which are less robust than found with endotoxin.

Increasingly, depression is viewed along a continuum of affective responses that lead to symptom expression, as opposed to being a categorical, diagnostic construct, and endotoxin affects the two cardinal affective symptoms that constitute depression: depressed mood and anhedonia. Endotoxin induces increases in depressed mood (Profile of Mood States [POMS]>3), and these responses are nearly 2-fold greater and within the range of clinical severity in those with sleep disturbance. Similarly, endotoxin induces increases depressive symptoms as indexed by the Montgomery-Asberg Depression Rating Scale (MADRS > 7), indicating mild depression, and these responses are attenuated by pretreatment with the antidepressant citalopram^73. Anhedonia (i.e., the lack of pleasure) also increases in response to endotoxin. Finally, endotoxin administration induces acute changes in the activity of neural substrates that are linked to depression. For example, the dorsal anterior cingulate cortex (dACC) and its functional connectivity to other regions are recognized for their role in the pathophysiology of depression. Endotoxin induces increases in activity of the dACC, which are

correlated with increases in inflammatory cytokines and reports of depressed mood . Moreover, endotoxin administration also reduces neural activity in the ventral striatum, a reward-related neural region , and decreased ventral striatum activity mediates effects of endotoxin on increases in depressed mood .

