Perceived social support is characterized by the Social Support Questionnaire Scale , Two-way Social Support Questionnaire , the Attachment Style Questionnaire , Social Provision Scale , and Experiences in Close Relationships Questionnaire . There is evidence that perceived social support, social connection, and social reward change in response to endotoxin .

Perceived social status is evaluated the using MacArthur Scale of Subjective Social Status (i.e., Social Ladder) .

Sensitivity to social rejection is examined by Fear of Negative Evaluation Scale  and the Rejection Sensitivity Scale . During the experimental protocol, we also administer a behavioral task, the Cyberball Social Exclusion Task . This task is administered only once at 2 hours after endotoxin vs. placebo, because it involves deception; no other real participants are engaged in this task as participants are led to believe prior to the task.

*Secondary outcome: cognitive processing.* Inflammatory challenge acutely alters measures of cognitive performance, including spatial learning and memory . We will use the virtual Morris Water Maze task  to assess computerized spatial learning and memory, followed by a Room Reconstruction Task  to assess the ability of cognitive mapping under real-life conditions. In addition, we assess several measures of cognitive processing and executive functioning, including the Cognitive Testing Stress Scale, the Spatial 2-Back Test, the Color Shape Task  and the Anti-saccade Task . The virtual Morris Water Maze and the Room Reconstruction Task are administered 2 hours following administration of endotoxin vs. placebo. Other cognitive measures are administered at baseline and 4 hours following administration of endotoxin vs. placebo.

*Secondary outcome: physical symptoms.* The Brief Symptom Inventory , which assesses a variety of somatic symptoms related to psychological distress is administered up to 5 hours following administration of endotoxin vs. placebo. Physical “sickness” symptoms which have been related to the administration of endotoxin are assessed using the Physical Symptom

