Questionnaire as described . These physical or “sickness symptoms” include self-reported rating of severity of muscle pain, shivering, nausea, breathing, difficulties, and fatigue are self-rated up to 12 hours.

*Secondary outcome: markers of inflammatory response.* Circulating levels of pro- and anti-inflammatory cytokines including IL-6, TNF, IL-8, IL-10 and IFN $\gamma$  are evaluated at baseline prior to the infusion, 30 and 60 minutes post infusion, and hourly for the remainder of the experimental protocol. Baseline levels of inflammation as indexed by CRP, and Toll-like receptor (TLR)-4 stimulated monocyte production of IL-6 and TNF, may be related to inflammatory responsiveness to challenge with endotoxin vs. placebo (i.e., inflammatory priming of the endotoxin response), and these measures will be obtained at baseline. We also examine upstream pathways related to activation of inflammatory cytokines using whole blood samples collected at baseline and 30, 60, and 120 minutes after infusion; RNA samples will be used to evaluate expression of genes involved in proinflammatory pathways (IL1B, IL6, IL8, CD83, CCL3, TNFAIP3, and NF- $\kappa$ B/Rel family) using quantitative real-time RT-PCR using established TaqMan Gene Expression Assays with transcriptional profiling of the Conserved Translational Response to Adversity (CTRA) in circulating peripheral blood mononuclear cells (PBMCs) .

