### *Statistical analysis*

Analyses will be reported according to the CONSORT statement, and will use Intent-To-Treat samples (i.e., all persons who were randomized and received either endotoxin or placebo will be included in the analysis). Measured baseline and outcome variables will be assessed for distributional qualities and transformed if necessary for use in the selected statistical models. All pre-classification variables, including age (60-70 years vs. 71-80 years), sex, and body mass

index (18-24.9 vs. 25–35 kg/m^2), as well as other baseline values will be compared between healthy controls and insomnia patients; those having a relationship with the outcome variables will be considered for inclusion as covariates in the main analyses. The detailed statistical analysis plan will be reviewed by the independent Trial Data Monitoring and Steering Committees of the UCLA Clinical Translational Sciences Institute. IBM SPSS Version 28, SAS version 9.4 or other established statistical packages will be used for all analyses.

The basic design is a 2 group (insomnia vs. comparison controls) by 2 condition (endotoxin vs. placebo), analysis variance (ANOVA) with one or more repeated measures of outcome analyzed with linear mixed models (LMM). LMM provides unbiased estimates when observations are missing at random. The timing repeated measures varies by assessment as noted above. The key results are the main effects of group, condition, and their interaction; for those analyses with repeated measures, the two main effects and interaction will further interact with the time variable.

*Primary Outcome: Depressed Mood.* The primary outcome is tested with LMM for the depressed mood subscale of the POMS and for severity of depressed mood and depressive symptoms of the MADRS with a time frame up to 12 hours.

*Secondary Outcome: Depressive Symptoms.* Change in depressive symptoms is tested with LMM for the clinician-rated assessment of depressive symptom severity as measured Hamilton Rating Scale for Depression with a time frame up to 8 hours.

*Secondary Outcome: Negative Affective Responding.* Change in negative affective responding is tested with LMM for the following behavioral tasks, Emotion Recognition Task and Emotion Intensity Task with a time frame of about 2 hours. Similar analytic strategy will be

applied for other secondary outcomes related to negative affect responding with time frames ranging from 4- to 12 hours.

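### The MADRS severity score, a primary outcome, may partly record endotoxin sickness rather than mood, and the protocol gives no way of telling the two apart on that scale

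*Protocol*

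**What the plan says.** Under Primary outcome, the protocol names the POMS for depressed mood and, with it, "observer-rated depressed mood and depressive symptom severity as measured by the MADRS". The Statistical analysis section repeats this: the linear mixed model is fitted to the depressed mood subscale of the POMS and to "severity of depressed mood and depressive symptoms of the MADRS with a time frame up to 12 hours". No MADRS item list, sub-score or adaptation to the acute setting is given. The only depression scale described as modified for acute use is the Hamilton scale, which is secondary.

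Under Secondary outcomes, the protocol describes "Physical “sickness” symptoms which have been related to the administration of endotoxin", measured by the Physical Symptom Questionnaire for up to 12 hours as "self-reported rating of severity of muscle pain, shivering, nausea, breathing, difficulties, and fatigue". Under cognitive processing it states: "Inflammatory challenge acutely alters measures of cognitive performance, including spatial learning and memory".

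The background section on the experimental model cites an earlier endotoxin response on the "Montgomery-Asberg Depression Rating Scale (MADRS > 7), indicating mild depression".

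**The concern.** The trial asks whether inflammation induces depression, and more so in people with insomnia. A depression scale that counts tiredness, poor concentration or poor appetite will rise when an intervention makes people feel ill, whether or not their mood falls. Randomisation, placebo and blinding do not remove this, because sickness is itself an effect of condition.

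At stake is how a positive MADRS result is interpreted. A rise driven by sickness could be reported as induced depressive symptoms. If insomnia also heightened the sickness response, part of a group by condition effect on the MADRS could be taken for vulnerability to depression.

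**Working it through.** The plan states no figure on this point, so there is nothing to reproduce. The check sets the passages side by side and then uses arithmetic as illustration.

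**1. Overlap between the scale and the sickness symptoms.** Assumption: the standard 10-item MADRS, each item scored 0 to 6.

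| MADRS item (assumed) | What the protocol says about endotoxin or inflammatory challenge | Support |
|---|---|---|
| Lassitude | Fatigue is a listed sickness symptom | Direct |
| Concentration difficulties | Cognitive performance is altered; spatial learning and memory are the examples | Indirect |
| Reduced appetite | Nausea is a listed sickness symptom | Indirect |

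**2. Weight of these items.** 3 × 6 = 18 of 10 × 6 = 60 points. A rating of 3 on each gives 3 × 3 = 9, above the threshold of 7 that the background calls mild depression, with every mood item at zero. The document does not say what ratings to expect, so this shows only what is possible.

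**3. Endotoxin contrast.** The Sample size section gives 80 per condition. Assume that only the three items rise, by x points each, and that the SD of the total is 4 to 8. The document gives neither x nor the SD. At one time point, two-sided alpha 0.05:

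P(p<0.05) = Φ(3x / (SD × √(2/80)) − 1.96)

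| x per item | Shift in total | SD 4 | SD 6 | SD 8 |
|---|---|---|---|---|
| 0.5 | 1.5 | 0.66 | 0.35 | 0.22 |
| 1 | 3 | 0.997 | 0.885 | 0.66 |
| 2 | 6 | 1.00 | 1.00 | 0.997 |

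For example, x = 1 and SD 6: 3 / (6 × 0.158) = 3.16; 3.16 − 1.96 = 1.20; Φ(1.20) = 0.885.

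**4. Group by condition contrast.** Trial Design gives 60 with insomnia and 100 controls, randomised 1:1 within group, so the cells are 30, 30, 50 and 50. At one time point:

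- SE = SD × √(2/30 + 2/50) = 0.3266 SD.
- Difference needed for 80% power = (1.96 + 0.84) × 0.3266 SD = about 0.91 SD.
- For SD 4 to 8 this is 3.7 to 7.3 points, or 1.2 to 2.4 points on each of the three items, over and above the sickness response of the controls.

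Repeated measures would lower this somewhat. The interaction is thus much less exposed than the endotoxin contrast.

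**5. What the planned analyses separate.** The sickness ratings are analysed as an outcome of their own. The pre-specified secondary analyses cover sex, past depression, cytokines as predictors of the outcomes, and mediation by inflammation for POMS Depression. None splits the MADRS by item type or sets it beside the sickness ratings.

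**The case against.** The strongest reply is that the trial already has a primary measure confined to mood. If endotoxin caused sickness only, the MADRS would rise and the POMS depressed mood subscale would stay flat, and the discrepancy would show in the primary results. Anhedonia, reward and facial-emotion measures are also collected. This stands in large part: the data needed to separate mood from sickness exist. What is missing is a stated rule for reading a MADRS effect that the POMS does not share.

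Item scoring may also be set out in a statistical analysis plan that is not shown, and neither the items nor the use of a total is printed in the protocol. That is why both are assumptions here. The choice of symptom severity as primary, however, is made in the protocol.

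The protocol also argues that the MADRS is sensitive to mood change after endotoxin, and that "these responses are attenuated by pretreatment with the antidepressant citalopram". Sensitivity is not specificity, and the document does not say which items responded, so this does not settle the matter.

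A reader might infer something stronger: that endotoxin directly causes all three symptoms, that a sickness response would make the interaction significant, and that the MADRS score should be replaced as primary. The documents do not support this. Only fatigue is directly documented. No passage says that insomnia heightens sickness, although the Overview expects heightened inflammatory responding; the interaction could be inflated, but significance is not shown. The stated construct expressly includes symptom severity, and the document offers no validation of a sub-score as its replacement.

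**Conclusion.** The concern holds in a limited form. An endotoxin effect on MADRS symptom severity could partly reflect sickness, most clearly through fatigue, and the protocol has no analysis or reading rule that would show it. The group by condition effect is possibly exposed too, but would need a large excess of sickness in the insomnia group.

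The share of any MADRS rise that comes from sickness is unknown; the probabilities above depend on assumed item shifts and SDs and show possibility, not expectation. The conclusion also rests on the standard item content and on severity meaning the summed score. The POMS depressed mood subscale is not affected. This is a cheap improvement to interpretation and no reason to discard the MADRS as an outcome.

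**What to change.** Keep the MADRS severity score as planned. Pre-specify the same linear mixed model on two parts of it:

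- (a) the affective items: sadness (apparent and reported), inability to feel, and pessimistic thoughts;
- (b) the lassitude, concentration and appetite items.

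Report both beside the Physical Symptom Questionnaire over the same hours. State in advance that a MADRS effect is interpreted as depressed mood only if the affective-item score or the POMS depressed mood subscale agrees, and what counts as agreement. Otherwise report it as possibly due to sickness. Apply the same rule to the group by condition effect.

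Do not adjust for sickness as a simple covariate. It arises after randomisation and is affected by condition, so the adjusted contrast would no longer be a clean randomised comparison.

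The cost is a few extra analyses of items already rated. The downside is that the affective sub-score is less standard than the full scale and may show a smaller effect.

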### Secondary outcomes:

*Secondary outcome: severity of depressive symptoms.* Change in severity of depressive symptoms is assessed by the observer-rater administration of the Hamilton Rating Scale for

Depression (HAMD), modified for administration during an acute time period with repeated assessment over up to 7 hours.

*Secondary outcome: negative affective responding.* Two tasks evaluate changes in negative affective responding: Emotion Recognition Task and Emotion Intensity Task, which are administered at baseline and again about 3 hours after endotoxin vs. placebo.

The Emotion Recognition Task evaluates the ability of participants to recognize an expressed facial emotion, and to rate their certainty in this choice. Delayed recognition of a sad emotion, for example, indicates a reduced sensitivity to sad facial expressions. Facial images are taken from video-recordings of the Cohn-Kanade facial expression database (Kanade et al., 2000; Lucey et al., 2010). Images represent a range of age, sex, and ethnicity, which are distributed equally across the emotions being assessed. In total, 7 trials are used, each comprising 10 images. Within each trial, the 10 images gradually progress from a neutral expression to a specific emotion. The trials (i.e., happy, sad, angry, afraid, surprised, and neutral) are presented in a random order. After each image, which is shown as 3-sec stimuli, participants are asked to identify the presented emotion (i.e., “Which emotion is this person feeling right now?”), and answers are collected during a 10-sec response (i.e., happy, sad, angry, afraid, surprised, or nothing yet). Task performance is indexed by the number of elapsed images (i.e., delay) required to correctly identify a contiguous sequence of images, with more elapsed images (i.e., longer delays) indicating attenuated or impaired facial emotion processing. A contiguous sequence was defined as a continuous series of consistently correct answers that led up to the full emotion expression (e.g., if a participant gave a correct answer for image #1 and #2, then an incorrect answer for image #3 to #6, and again a correct answer for image #7 to #10, the delay for this trial was determined as “7”, because the onset of the contiguous sequence that led up to the full emotion expression started at image #7). This analytical approach has the advantage of providing more stringent recognition criteria, as opposed to capturing impulsive responding. Whereas it is known that sleep disturbance is associated with

subjective reports of negative affect, there are few empirical studies that have examined tasks of emotional processing, even though accurate face judgments may modulate emotional reactivity. We have previously found that sleep disturbance is associated with a delay in recognition of sad facial emotion in older adults .

The Emotion Intensity Task evaluates subjective ratings of perceived intensity in response to various degrees of facially-expressed sadness, happiness, and anger  taken from NimStim set of facial affects  and includes sad, happy, and angry and a neutral face of one white male individual. Each emotion image morphes with the neutral image using a face-morph software (Morph 2.5), resulting in 10 images covering a range of emotion expression (i.e., image #1 reflects 10% emotion expression, image #2 reflects 20% emotion expression, etc.). In total, 10 separate images are created for each emotional category, which represents the full range of emotion expression. The trials (i.e., sadness, happiness, anger) are presented in a random order. Prior to each trial, participants are informed which specific emotion they are about to rate for intensity (e.g., “You are about to see a sad face”), and are familiarized with the full range of emotion expression. During the task itself, each emotion is presented in a separate trial, and within each trial, the 10 images were presented in a random order as 2-sec stimuli. During the three trials, participants are presented with a morphing image and are asked to identify the emotion as soon as they recognize which emotion being depicted. The image gradually progresses from neutral to the specific emotion. The participant is presented with a red “x” if the incorrect emotion is chosen. Task performance is indexed by the mean rating across the 10 images within each trial, with lower ratings indicating lower perceived intensity. Hence, Emotion Intensity Task differs from the Emotion Recognition Task; the Emotion Intensity Task evaluated the perceived intensity to a known emotion, whereas Emotion Recognition Task evaluates the ability to recognize or identify an emotion.

*Secondary outcome: positive affective responding.* Two tasks will be used to evaluate changes in positive affective responding: Probabilistic Reward Task (PRT) and the Effort

Expenditure for Rewards Task (EEfRT), which are administered about 2.5 hours after endotoxin vs. placebo.

The PRT is a laboratory based probabilistic reward task that objectively measures participants' ability to modulate behavior as a function of reward. This task has been found to identify reduced reward learning in depressed patients which is state-dependent and also to predict the persistent diagnosis of depression in the midst of treatment. The method of this computerized reward-learning task is extensively described. This task was selected because anhedonia is a core feature of major depressive disorder and includes a reduction in experienced pleasure (liking reward) and dysfunction in reward anticipation and reward learning. We have previously found that an inflammatory challenge reduces neural sensitivity to reward anticipation. There are limited data on the relationship between insomnia on reward responsiveness, although individuals with insomnia show reduced positive affect using ecological momentary assessment.

The Effort Expenditure for Rewards Task (EEfRT) is used to evaluate reward processing. The EEfRT is a computerized task that assesses effort-based decision making in the context of monetary reward. During the task, participants are presented with a series of trials in which they choose between an easy, low effort trial (worth a low reward amount of \$1.00) and a hard, high effort trial (worth higher reward amounts ranging between \$1.24-\$4.30). Easy trials required 30 button presses using the index finger of the non-dominant hand in 7 seconds, while hard trials required 100 button presses with the pinky finger of the dominant hand in 21 seconds. Participants are told that not all successfully completed trials are rewarded, and the probability that a successful response yields a reward (12%, 50%, 88%) is presented for each trial. In the current study, the EEfRT is shortened from 20 minutes to 10 minutes and hard trials used the pinky finger of the dominant hand rather than the non-dominant hand to accommodate constraints in the laboratory environment. Motivation for reward on the EEfRT is operationalized by willingness to exert effort for monetary reward; i.e., the selection of high

effort/high reward trials relative to the selection of low effort/low reward trials. Sensitivity to reward is operationalized by the association between changes in monetary reward magnitude (ranging from \$1.24-\$4.30) and changes in likelihood of selecting high effort/high reward trials vs. low effort/low reward trials.

Other secondary outcomes related to positive affective responding include measures of interest in activities and reward responsiveness, as well as responding to social reward. Three self-report questionnaires are used to evaluate interest in activities, reward responsiveness, or hedonic experience, including Snaith-Hamilton Pleasure Scale (SHAPS), and the Temporal Experience of Pleasure Scale,. These questionnaires are administered at baseline and about 4 to 5 hours after endotoxin vs. placebo.

To evaluate social reward, we use a social reward task (i.e., Emotional Dot Probe task with happy faces) and a questionnaire (i.e., Close Other Social Reward) to evaluate change in social reward before and after inflammatory challenge with endotoxin vs. placebo. We have previously found that inflammatory challenge reduces reward activation to non-social reward cues, but increases activation to social reward. The task is administered at baseline and about 1.5 hour after endotoxin vs. placebo, and the questionnaire is administered at baseline and 4 hours after endotoxin vs. placebo.

*Secondary outcome: social domain* Because social factors contribute to depression in part by changes inflammatory mechanisms, this study examines several aspects related to social connection and loneliness, social support, and sensitivity to social rejection. Perceived social connection is evaluated at baseline and repeatedly for up to 12 hours, whereas other measures are obtained at baseline and up to 5 hours after endotoxin vs. placebo.

Perceived social connection is evaluated with several self-report questionnaires including How I Feel Right Now, which includes Feelings of Social Disconnection, and the 10-item Revised UCLA Loneliness Scale.

Perceived social support is characterized by the Social Support Questionnaire Scale , Two-way Social Support Questionnaire , the Attachment Style Questionnaire , Social Provision Scale , and Experiences in Close Relationships Questionnaire . There is evidence that perceived social support, social connection, and social reward change in response to endotoxin .

Perceived social status is evaluated the using MacArthur Scale of Subjective Social Status (i.e., Social Ladder) .

Sensitivity to social rejection is examined by Fear of Negative Evaluation Scale  and the Rejection Sensitivity Scale . During the experimental protocol, we also administer a behavioral task, the Cyberball Social Exclusion Task . This task is administered only once at 2 hours after endotoxin vs. placebo, because it involves deception; no other real participants are engaged in this task as participants are led to believe prior to the task.

*Secondary outcome: cognitive processing.* Inflammatory challenge acutely alters measures of cognitive performance, including spatial learning and memory . We will use the virtual Morris Water Maze task  to assess computerized spatial learning and memory, followed by a Room Reconstruction Task  to assess the ability of cognitive mapping under real-life conditions. In addition, we assess several measures of cognitive processing and executive functioning, including the Cognitive Testing Stress Scale, the Spatial 2-Back Test, the Color Shape Task  and the Anti-saccade Task . The virtual Morris Water Maze and the Room Reconstruction Task are administered 2 hours following administration of endotoxin vs. placebo. Other cognitive measures are administered at baseline and 4 hours following administration of endotoxin vs. placebo.

*Secondary outcome: physical symptoms.* The Brief Symptom Inventory , which assesses a variety of somatic symptoms related to psychological distress is administered up to 5 hours following administration of endotoxin vs. placebo. Physical “sickness” symptoms which have been related to the administration of endotoxin are assessed using the Physical Symptom

Questionnaire as described . These physical or “sickness symptoms” include self-reported rating of severity of muscle pain, shivering, nausea, breathing, difficulties, and fatigue are self-rated up to 12 hours.

*Secondary outcome: markers of inflammatory response.* Circulating levels of pro- and anti-inflammatory cytokines including IL-6, TNF, IL-8, IL-10 and IFN $\gamma$  are evaluated at baseline prior to the infusion, 30 and 60 minutes post infusion, and hourly for the remainder of the experimental protocol. Baseline levels of inflammation as indexed by CRP, and Toll-like receptor (TLR)-4 stimulated monocyte production of IL-6 and TNF, may be related to inflammatory responsiveness to challenge with endotoxin vs. placebo (i.e., inflammatory priming of the endotoxin response), and these measures will be obtained at baseline. We also examine upstream pathways related to activation of inflammatory cytokines using whole blood samples collected at baseline and 30, 60, and 120 minutes after infusion; RNA samples will be used to evaluate expression of genes involved in proinflammatory pathways (IL1B, IL6, IL8, CD83, CCL3, TNFAIP3, and NF- $\kappa$ B/Rel family) using quantitative real-time RT-PCR using established TaqMan Gene Expression Assays with transcriptional profiling of the Conserved Translational Response to Adversity (CTRA) in circulating peripheral blood mononuclear cells (PBMCs) .

